#### Interventions

All exercise interventions are 12-week programmes, comprised of 3 × 50-min sessions per week. All sessions will be supervised by trained exercise monitors/instructors (monitor: participant ratio 1:1) and will start and end with warm-up and cool-down exercises (i.e. low-intensity cycling or cross trainer, general whole body movements and stretches).

##### Aerobic

This intervention consists of 3 × 50-min sessions per week of progressive continuous aerobic exercise, completed on a cross-trainer or stationary bike or combination of both. Over the course of weeks 1 to 6, session length will gradually increase (in 5-min blocks) until participants can perform 3 × 50-min sessions in week 7. The programme will progressively increase in intensity from weeks 1 to 12 (Table 3), starting at an intensity of 40–50% HRR (weeks 1–2) and finishing at an intensity of 75–80% HRR (weeks 11–12). Participants will wear heart rate monitors and use the RPE scale to monitor intensity levels (make: Garmin; model: Forerunner 45).

**Table 3 Tab3:** Progression plan from week 1 to week 12 for all exercise groups

Summary description of exercise interventions [frequency, intensity, time and type (F.I.T.T.)]						
Trial arm	Weeks 1–2	Weeks 3–4	Weeks 5–6	Weeks 7–8	Weeks 9–10	Weeks 11–12
Aerobic	3 sessions/week Low Intensity (40–50% HRR)^a^ Continuous aerobic exercise 20–30 min^b^	3 sessions/week Low–moderate intensity (50–55% HRR)^a^ Continuous aerobic exercise 30–40 min^b^	3 sessions/week Low–moderate Intensity (55–60% HRR)^a^ Continuous aerobic exercise 40–50 min^b^	3 sessions/week Moderate intensity (60–70% HRR)^a^ Continuous aerobic exercise 50 min	3 sessions/week Moderate–vigorous intensity (70–75% HRR)^a^ Continuous aerobic exercise 50 min	3 sessions/week Vigorous intensity (75–80% HRR)^a^ Continuous aerobic exercise 50 min
Resistance	3 sessions/week Low load (40–50% 1-RM)^a^ Resistance training 20–30 min^b^ 2 × 12 reps (6 exercises)	3 sessions/week Low–moderate load (50–55% 1-RM)^a^ Resistance training 30–40 min^b^ 3 × 12 reps (6 exercises)	3 sessions/week Low-moderate load (55–60% 1-RM)^a^ Resistance training 40–50 min^b^ 3–6 × 12 reps (6 exercises)	3 sessions/week Moderate load (60–65% 1-RM)^a^ Resistance training 50 min; 3–6 × 12 reps (6 exercises)	3 sessions/week Moderate–high load (70–75% 1-RM)^a^ Resistance training 50 min; 3–6 × 12 reps (6 exercises)	3 sessions/week High load (75–80% 1-RM)^a^ Resistance training 50 min; 3–6 × 12 reps (6 exercises)
Combined	3 sessions/week **Aerobic component** Low intensity (40–50% HRR)^a^ Continuous aerobic exercise 10–15 min **Resistance component** Low load (40–50% 1-RM)^a^ Resistance training 10–15 min; 2 × 12 reps (3 exercises)	3 sessions/week **Aerobic component** Low–moderate intensity (50–55% HRR)^a^ Continuous aerobic exercise 15–20 min **Resistance component** Low–moderate load (50–55% 1-RM)^a^ Resistance training 15–20 min; 3 × 12 reps (3 exercises)	3 sessions/week **Aerobic component** Low–moderate Intensity (55–60% HRR)^a^ Continuous aerobic exercise 20–25 min **Resistance component** Low–moderate load (60–70% 1-RM)^a^ Resistance training 20–25 min; 3–6 × 12 reps (3 exercises)	3 sessions/week **Aerobic component** Moderate intensity (60–70% HRR)^a^ Continuous aerobic exercise 25 min **Resistance component** Moderate load (65–70% 1-RM)^a^ Resistance training 25 min; 3–6 × 12 reps (3 exercises)	3 sessions/week **Aerobic component** Moderate–vigorous intensity (70–75% HRR)^a^ Continuous aerobic exercise 25 min **Resistance component** Moderate–high load (70–75% 1-RM)^a^ Resistance training 25 min; 3–6 × 12 reps (3 exercises)	3 sessions/week **Aerobic component** Vigorous intensity (75–80% HRR)^a^ Continuous aerobic exercise 25 min **Resistance component** High load (75–80% 1-RM)^a^ Resistance training 25 min; 3–6 × 12 reps (3 exercises)

^a^Sessions will increase in intensity/load by 2.5–5% as tolerated between sessions during weeks 1–12 up to the max intensity/load for the fortnightly block, provided the duration (during weeks 1–6) remains the same for the sessions where intensity/load is changed

^b^Sessions will increase in duration by 5 min during weeks 1–6 up to the max time for that fortnightly block, provided the intensity/load remains the same for the session where duration is increased

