##### Combined

This intervention will consist of 3 × 50-min sessions per week comprising of 25 min of progressive aerobic exercise (cross trainer, cycling) and 25 min (three exercises: one upper limb, one core, one lower limb) of a progressive resistance programme (Table 4). The resistance portion of this intervention can include any of the eighteen exercises outlined in the resistance intervention above. However, the prescription of compound exercises (bench press, squat etc.) will be prioritised each week over the inclusion of any single joint movements (i.e. triceps exercises). In line with the aerobic and resistance trial arms, both components (aerobic and resistance) of the combined intervention will increase in load/intensity across the 12 weeks from 40% 1RM/HRR in week 1 to 80% 1RM/HRR in week 12 (Table 3).

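### Table 3 sets heavier resistance loads for the combined arm than for the resistance arm in weeks 5–8, under the same labels and without a reason

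*Protocol article*

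**What the plan says.** Table 3 sets out a fortnightly progression for each exercise arm. For the resistance arm it prescribes "Low-moderate load (55–60% 1-RM") in weeks 5–6 and "Moderate load (60–65% 1-RM") in weeks 7–8. For the resistance component of the combined arm it prescribes "Low–moderate load (60–70% 1-RM") and "Moderate load (65–70% 1-RM") in the same two blocks.

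Footnote a to the table lets intensity or load rise in small steps, as tolerated, "up to the max intensity/load for the fortnightly block".

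The Combined section describes the relation between the arms this way: "In line with the aerobic and resistance trial arms, both components (aerobic and resistance) of the combined intervention will increase in load/intensity". It gives the start and end points as 40% and 80% of 1RM or HRR and refers to Table 3.

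Under Hypotheses tested, the secondary null hypothesis compares the aerobic, resistance and combined groups with one another on CRF, strength and body composition.

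**The concern.** The two arms appear to share one loading scheme, except in two adjacent blocks where the combined arm is heavier. The labels do not change with the numbers, and no section gives a reason.

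As written, the resistance and combined arms differ in more than the split between modalities and the planned resistance volume (six exercises per session against three). They also differ in prescribed relative load for a third of the programme. That is a second, undeclared contrast inside the secondary comparison, and strength is one of its outcomes. The pilot also reports adherence to the prescribed programme, so the prescription should be unambiguous. A definitive trial that reused Table 3 would inherit the mismatch.

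**Working it through.** **Inputs.** All ranges come from the Resistance and Combined rows of Table 3 (% 1-RM). Midpoint = (lower + upper) / 2. The ceiling is the upper limit of the range, as footnote a implies.

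| Weeks | Resistance arm | Combined arm, resistance part | Midpoints | Midpoint difference | Ceiling difference |
|---|---|---|---|---|---|
| 1–2 | 40–50 | 40–50 | 45 / 45 | 0 | 0 |
| 3–4 | 50–55 | 50–55 | 52.5 / 52.5 | 0 | 0 |
| 5–6 | 55–60 | 60–70 | 57.5 / 65 | +7.5 | +10 |
| 7–8 | 60–65 | 65–70 | 62.5 / 67.5 | +5 | +5 |
| 9–10 | 70–75 | 70–75 | 72.5 / 72.5 | 0 | 0 |
| 11–12 | 75–80 | 75–80 | 77.5 / 77.5 | 0 | 0 |

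**Relative size.** Weeks 5–6: 65 / 57.5 = 1.13, about 13% heavier. Weeks 7–8: 67.5 / 62.5 = 1.08, 8% heavier. In each block the two ranges meet only at an end point (60% and 65%).

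**Average over the programme.**
- Resistance arm: (45 + 52.5 + 57.5 + 62.5 + 72.5 + 77.5) / 6 = 367.5 / 6 = 61.25%.
- Combined arm: (45 + 52.5 + 65 + 67.5 + 72.5 + 77.5) / 6 = 380 / 6 = 63.33%.
- Difference: 12.5 / 6 = 2.08 percentage points.

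**Exposure.** 4 weeks × 3 sessions = 12 sessions, out of 12 × 3 = 36.

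**The aerobic side as a comparison.** The combined arm's aerobic component matches the aerobic arm in all six blocks, including "Low–moderate Intensity (55–60% HRR") in weeks 5–6 and "Moderate intensity (60–70% HRR") in weeks 7–8. So 10 of the 12 paired cells (six aerobic, six resistance) agree, and the two exceptions are adjacent.

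**Signs of a slip.**
- In weeks 5–6, three of the four progressions in the table (aerobic, resistance, combined-aerobic) read 55–60%. Only combined-resistance reads 60–70%.
- The four progressions have 4 × 5 = 20 block-to-block steps. The ceiling rises in 19 of them. The exception is combined-resistance from weeks 5–6 to weeks 7–8, where it stays at 70%.
- Low–moderate load reaches 70% in the combined row, above the 65% ceiling of moderate load in the resistance row.
- The resistance row jumps from 60–65% to 70–75% and never uses 65–70%, so its weeks 7–8 cell may also be wrong.

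These signs suggest an error but do not prove one, and they do not settle which row is wrong.

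**The case against.** The strongest reply is that nothing stated is actually broken. The Combined section spells out only the 40% and 80% end points, and both rows meet them. The interventions are described as matched on time, and equal relative load in each block is never claimed. The combined arm already does half the resistance minutes with half the exercises, so four weeks of somewhat higher % 1-RM adds little.

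The figures are also nominal. Load rises only as tolerated and under one-to-one supervision, and several core exercises use body weight, where % 1-RM means little. The 12-week average difference of 2.1 points is below the smallest progression step in footnote a (2.5%). The trial is a feasibility pilot that disclaims power for between-group comparisons, and loads are identical in the four weeks before follow-up.

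Much of this stands. The wording on progressing in line is loose and does not promise identical blocks. The midpoint differences describe what is prescribed, not what is lifted. The effect on the pilot's main results is small.

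It does not remove the inconsistency. The same label carries two different ranges, the other ten paired cells agree, and no rationale is offered. Being matched on time does not explain why load should differ in two blocks only. Because the footnote makes the ranges working ceilings, instructors following the table would apply different limits in the two arms.

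**Conclusion.** The point holds, as a minor one. Table 3 prescribes a heavier relative load for the combined arm than for the resistance arm in weeks 5–8, with ceilings 10 and then 5 percentage points higher, over 12 of 36 sessions. The 12-week average midpoint is about 2.1 points higher.

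These sizes assume that the block ranges are followed and that the midpoint represents the range. Tolerance-based progression could make the delivered difference smaller. The mismatch itself is certain. Whether it is a slip or a deliberate choice cannot be settled from the document. It does not touch the sample size, the error rates, or the recruitment, retention and attendance results. It does put an unexplained load difference into the resistance-versus-combined comparison.

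**What to change.** Use one common set of % 1-RM ranges for weeks 5–8 in the Resistance and Combined rows, confirmed by the clinical team. Two candidates:

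- **55–60% then 60–65%.** The combined row follows the resistance row. Two cells change.
- **55–60% then 60–70%.** Both rows take the same numerical steps as the aerobic row and run without gaps or overlaps. Three cells change, including the resistance arm's weeks 7–8. HRR and 1-RM are different scales, so this is a convenience and not a requirement.

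If the heavier combined-arm load is intended, state that in Table 3, give the reason, and qualify the wording in the Combined section. This is the weaker remedy, because the load difference then stays in the comparison.

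The cost is two or three table cells, or one explanatory sentence. Randomisation, outcomes and analysis are unchanged.

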##### Resistance

This intervention consists of 3 × 50-min sessions per week of progressive resistance exercises. During weeks 1–6, session length will gradually progress until participants can perform 3 × 50-min sessions in week 7 (Table 3). The resistance programme contains eighteen exercises, with an equal amount of upper limb (shoulder press, bench press, bicep curl, raise, triceps exercises, bent-over row) core (seated and standing twists, hip bridge, 4-point kneel, overhead ball slam, push-ups) and lower limb (barbell squat, goblet squat, deadlift, Romanian deadlift, lunge, lateral lunge) exercises included. In each session, participants will perform six exercises aimed at targeting all major muscle groups (Table 4). The participants will perform three different exercise regimes on a weekly basis, alternating every second week (Table 5). They will be monitored to track weights lifted and be provided with feedback on correct technique as needed. In weeks 1–2, participants will perform 2 × 12 reps of the six exercises at 40–50% 1RM to allow them to become familiar with the different exercises. From weeks 3 to 4, participants will perform 3 × 12 reps of each exercise at 50–55% 1RM. From weeks 5 to 12, participants will perform up to six sets of each exercise to meet the prescribed time for each session (i.e. 50 min). The load will progressively increase for all exercises performed from weeks 1–12 from 40% 1RM in week one to 80% 1RM in week twelve (Table 3) once a participant can perform all sets of 12 reps with proper form in one session and/or once the participant reports finding the exercise easy. Each set of exercises will be followed by a 45-s rest.

**Table 4 Tab4:** Resistance exercises included in the resistance and combined programmes

Exercise	Variations
**Upper body**	
Bench press^a^	Standard flat bench press with BB/DB Incline bench press with BB/DB Grip: wide, normal, narrow
Shoulder press	Overhead press with DB BB press Grip: wide, narrow Position: standing, seated
Bent over row	Standard BB row Single arm supported row with DB/KB
Raise	Forward raise Lateral raise Bent over fly Resistance: DB, weight plate
Bicep exercises	Curl with DB Curl with BB Position: standing, seated Grip: Supine, ‘hammer’, alternating supine and prone (‘Zottman’ curl)
Triceps exercises	Standing/seated behind the head extensions without resistance or 2xDB Lying triceps extensions French press with DB/KB Bench dips (BW or weight plate) KB/DB halos
Kettlebell swings	Two-hand ‘Russian’ swing Alternating swing Single hand swing Overhead ‘American’ swing
**Core**	
Push-ups	Wall push-up Elevated push-up on bench Push up on knees Push up on KB Standard push-up Position: wide hand position, narrow hand position
Seated twist	Sitting with legs supported BW Sitting with legs supported with medicine ball/ KB Sitting with legs lifted off ground and crossed BW Sitting with legs lifted off ground and crossed with medicine ball/ KB) Sitting with legs lifted off ground and held together (BW, with medicine ball/ KB)) Position: variance in torso lean back
Overhead medicine ball slam	Position: depth of squat Resistance: weight of medicine ball
Hip bridge	Two-legged bridge BW Two-legged bridge with resistance (DB, weight plate or bar) Single leg bridge with heel support of other foot Single leg bridge
4-point kneel (swimming exercise)	Slide one leg back along mat with/ without leg lift Opposite hand opposite leg (with hand still in contact with mat) Opposite hand opposite leg lift With weight plate in hand Pull-through with KB/DB/weight plate
Opposite leg touch (standing twist)	Twist to touch opposite knee up Twist to touch opposite leg kicked out Twist with weight plate in hand
**Lower body**	
Squat^a^	Chair/bench squat (BW, with KB/DB, with BB) DB/KB ‘Goblet’ squat BB Back squat BB Front Squat Split squat (one foot behind on floor; one foot supported on bench) Foot position: hip width, sumo (wide)
Lunges	Forward/reverse/side lunge Resistance: BW, Single DB/KB held in front; double DB/KB racked at shoulder or held down by sides; BB on back Position: stationary, walking lunge
Deadlift	Standard BB deadlift Sumo deadlift Romanian deadlift with DB or BB
Kettlebell swings	Two-hand ‘Russian’ swing Alternating swing Single hand swing Overhead ‘American’ swing

*BB* barbell, *BW* body weight, *DB* dumbbell, *KB* kettlebell

^a^All participants in resistance or combined programme will squat/bench or progress to squat/bench with BB unless limited physically (i.e. by injury etc.). Variations with KB/DB will be used during consecutive sessions for bench/squat

**Table 5 Tab5:** Sample exercise plan

Week ‘A’		
**Session 1** Bench press with BB Bent over row Seated twist Overhead ball slam Squat with KB/DB Side lunge	**Session 2** Shoulder press Raise/KB swing Push-up Hip bridge Squat with BB Romanian deadlift	**Session 3** Biceps exercises Triceps exercises Standing twist 4-point kneel Deadlift with BB Lunge
Week ‘B’		
**Session 1** Shoulder press Biceps exercises Push-up Seated twist Squat with BB Romanian deadlift	**Session 2** Bench with BB Raise/KB swing 4-point kneel Hip bridge Squat with DB/KB Lunge	**Session 3** Bent over row Triceps exercises Standing twist Overhead ball slam Deadlift with BB Side lunge

##### Combined

This intervention will consist of 3 × 50-min sessions per week comprising of 25 min of progressive aerobic exercise (cross trainer, cycling) and 25 min (three exercises: one upper limb, one core, one lower limb) of a progressive resistance programme (Table 4). The resistance portion of this intervention can include any of the eighteen exercises outlined in the resistance intervention above. However, the prescription of compound exercises (bench press, squat etc.) will be prioritised each week over the inclusion of any single joint movements (i.e. triceps exercises). In line with the aerobic and resistance trial arms, both components (aerobic and resistance) of the combined intervention will increase in load/intensity across the 12 weeks from 40% 1RM/HRR in week 1 to 80% 1RM/HRR in week 12 (Table 3).

##### Control

The control group will be instructed to maintain their physical activity levels for the 12-week intervention period. After this period, all participants randomised to the control group will be offered the opportunity to join one of the three exercise groups as per their preference to avail of an individualised and supervised exercise programme for 12 weeks.

#### Sample size

As this is a pilot study, which has the primary goal of evaluating the feasibility of the interventions and not ensuring there is adequate power to detect between-group differences, a formal sample size calculation is not required [48]. However, the researchers recognise that the sample size will need to be large enough to provide a degree of accuracy around the estimated effect of the interventions on a desired outcome (i.e. between-group difference in CRF which would be the primary outcome in an RCT) which would indicate whether a definitive RCT is worth pursuing. We estimated that we would need to recruit approximately 10% of the number of participants needed for a full-scale RCT. Based on previous research in this area [67], a sample size calculation for a definitive RCT indicates that we would need to recruit 484 participants. Therefore, allowing for 20% attrition, we aim to recruit 60 participants for this pilot study to inform the power analysis for a full-scale RCT.

#### Blinding

Blinding of participants to their group allocation will not be possible due to the nature of the interventions. However, all participants will be informed (information leaflet) that they have an equal chance of being randomly allocated to any one of the four groups. Once the intervention commences, blinding of the assessors and instructors will not be possible. However, the assessor and exercise instructors will not be involved in group allocation and will remain unaware of the unique participant numbers until completion of the data analysis. The trial statistician will also be unaware of group allocation until completion of data analysis.

#### Statistical methods

To evaluate the feasibility of the intervention, the number of eligible participants recruited, randomised and retained as well as dropouts lost to follow-up will be analysed as percentages. Data on participants attendance adherence to and compliance with prescribed interventions (i.e. average adherence to reps, sets, HR) will be analysed and the mean results reported as percentages. The incidence of adverse events (an adverse event defined as an event which a participant identifies a problem caused by the exercise programme that required the participant to seek treatment from a health professional and/or prevents participation in the programme) will also be analysed as percentages across all interventions. The acceptability of trial procedures based on participants’ experiences will be explored qualitatively as outlined in this protocol below. Feasibility data will be used to inform the development of a potential full-scale RCT.

In line with CONSORT guidance, the analysis of secondary outcomes will be conducted on an intention to treat basis. All data collected from participants (sociodemographic information, outcome questionnaire scores etc.) will be coded, cleaned and checked for errors. The data will then be entered into the Statistical Package for the Social Sciences (SPSS Version 26) for analysis. The study’s statistician ([name]) will remain blinded to group allocation until the analysis is complete. The change in mean values before and after intervention will be calculated for secondary outcomes. Analysis of variance (ANOVA) and *t*-tests will be applied to compare between-group and within group-differences at baseline and follow-up for each outcome. If there are sufficient participants (*n* = 60), the data will be analysed using analysis of covariance (ANCOVA) with the age and BMI as covariates. Statistical significance will be defined as *p* ≤ 0.05.

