### Aims and objectives

Therefore, the primary aim is to evaluate the feasibility and acceptability of prescribed time-matched aerobic, resistance and combined interventions (targeting changes in cardiorespiratory fitness) in women with obesity and to inform whether a future definitive trial could or should be undertaken. We will assess recruitment challenges; retention rates, attendance rates and adherence of participants to prescribed programme, incidence of adverse events and participant’s experience of the intervention and the acceptability of trial procedures and the programmes. We will also collect data from which a power calculation can be based to determine the number of participants needed per group in order to achieve significance in a potential follow-up randomised controlled trial (RCT).

The secondary objectives are to determine the mean difference between groups (three exercise groups and a non-exercise control group) at 12 weeks in:(i)CRF (predicted VO_2_ max)(ii)anthropometric outcomes (Body mass index (BMI), percentage body fat (%BF), lean mass (LM), fat mass (FM), waist-hip ratio (WHR) and waist circumference (WC)(iii)strength (five repetition maximum [5RM] bench press, leg dynamometry, grip strength)(iv)self-reported quality of life, physical activity, sedentary time, sleep, mood and pain

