##### Muscular strength

In order to measure strength, a 5RM bench press, leg dynamometry and grip strength will be used. To measure repetition maximum for bench press, participants will be instructed on proper form for this exercise and guided through progressive lifts where the weight will be increased in increments of 1.25–2.5 kg as needed until the participant reaches a weight at which they cannot perform all 5 reps of the movement maintaining good form. Fifty seconds of rest will be provided between attempts.

Leg strength will be measured using a back-leg strength dynamometer (Takei Back-D TKK 5402, Takei Scientific Instruments, Japan). Participants will be instructed to stand on the base of the machine, with feet shoulder width apart and their back bent slightly forward at the hips. The length of the chain will be adjusted so that the base of the bar rests superior to the anterior pole of the patella. Looking forward with a straight back, participants will be instructed to pull on the chain as hard as they can for 3 s in one fluid movement. Participants will be instructed to perform this test three times, with a rest of 50 s after each attempt. The maximum weight (kg) of all three attempts will be recorded. Grip strength will be measured using a hand-held dynamometer (Jamar Hydraulic Hand Dynamometer, Performance Health Supply, USA). To perform this measure, participants will be placed in sitting and the dominant arm supported on a side table and positioned with shoulder adducted, neutrally rotated, elbow flexed at 90°, forearm in neutral position and wrist between 0–30° dorsiflexion and 0–15° ulnar deviation [53]. The dynamometer handle will be set to the second handle position from the inside. Participants will be instructed to squeeze the handle for 3 s and will perform the test three times, with a rest of 50 s between attempts. The maximum weight (kg) of all three attempts will be recorded.

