##### Cardiorespiratory fitness

Given this study will recruit some high-risk participants (obesity class I: BMI 30–30.9 kg/m^2^, obesity class II: BMI 35–39.9 kg/m^2^ and obesity class III: BMI ≥ 40kg/m^2^) [51, 54] and in order to protect participant safety, a submaximal graded walking treadmill (make: h/p/cosmos; model: quasar) test will be conducted and used to estimate VO_2_ max. Guided by the Balke-Ware protocol for females [55], participants will warm-up for 4 min starting at a speed of 3.2km/hr and an incline of 0% and progressing to 3.8km/h by the end of the warmup, in line with the speed recommended for adults with obesity in the modified Balke protocol [56] With the speed remaining consistent, the gradient will then be increased by 2.5% every 3 min up until a gradient of 25%. If the participant has not achieved any of the criteria for test termination at this stage, the speed of the treadmill will then be increased by 0.3km/h every 3 min until they do so. The test will be deemed complete and terminated once the participant reaches 85% of their age-predicted HR_max_. Alternatively, the test will be terminated before the participant reaches 85% of age-predicted HR_max_ if (i) they report a rating of perceived exertion (RPE) ≥ 18 or (ii) reach volitional exhaustion. An RPE cut-off was included as a potential reason for test termination given that RPE ≥ 17–19 has both been utilised as a criterion for achieving VO_2_ max [57] and previously as a criterion for the termination of a submaximal Balke treadmill protocol in a clinical population [58, 59]. Furthermore, research indicates that RPE > 17 reasonably correlates with VO_2_ max and can be used to predict VO_2_ max with acceptable accuracy [60].

VO_2_ max will be estimated using the Fitness Registry and the Importance of Exercise National Database (FRIEND) equation (VO_2_ max = speed × (0.17 + fractional grade × 0.79) + 3.5) [61]. Gas exchange including O2 and CO2 concentrations, and respiratory exchange ratio (RER) will be measured using a gas analysis system (make: COSMED; make: Quark CPET, Rome, Italy). Heart rate will be measured every minute throughout the test by a heart rate monitor (make: Polar; model: Wind with WearLink chest belt). As CRF is being measured using a sub-maximal protocol, electrocardiograms will not be used during testing. Rating of perceived exertion (RPE) will be measured using the Borg RPE scale every minute of the test [62].

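### The adverse-event definition counts only problems the participant blames on the exercise programme, so the reported incidence is an attributed subset with no control-arm background rate and no cover for the test visits

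*Protocol article*

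**What the plan says.** The Aims and objectives section of the protocol article lists "incidence of adverse events and participant’s experience of the intervention" among the items assessed under the primary aim. The Abstract gives the main outcome as feasibility and acceptability of both the intervention and the procedures.

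The only definition of an adverse event is in Statistical methods. It is "an event which a participant identifies a problem caused by the exercise programme", and the problem must also be one that "required the participant to seek treatment from a health professional and/or prevents participation in the programme". The resulting incidence "will also be analysed as percentages across all interventions". The same section says that the feasibility data will inform a possible full-scale trial.

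Three other sections bear on who can have a countable event:

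- **Control:** "The control group will be instructed to maintain their physical activity levels for the 12-week intervention period". An exercise programme is offered to this arm only afterwards.
- **Muscular strength:** "In order to measure strength, a 5RM bench press, leg dynamometry and grip strength will be used". These tests are assessments, not part of the training programme.
- **Cardiorespiratory fitness:** "Given this study will recruit some high-risk participants", a submaximal graded treadmill test is used. Under Follow-up assessment, the same procedures are repeated once the intervention has ended.

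**The concern.** The definition sets three conditions at once: the participant must identify the problem, she must believe that the programme caused it, and it must have led to treatment or stopped her taking part. Causality is thus decided by an unblinded participant before anything is counted, and the article describes no recording of events that fail her attribution.

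A medical event that she does not connect with exercise is left out even if an investigator would have judged it related. Controls contribute nothing, so there is no background rate against which to read the exercise-arm figure. An injury or cardiovascular event at a test visit falls outside the definition, although the procedures are part of what the pilot is judging.

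The figure will be labelled as adverse-event incidence and will feed the decision on a larger trial in a population that the protocol itself calls partly high-risk. Events that are never asked about, in controls above all, cannot be reliably recovered later.

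**Working it through.** **Group sizes.** The article plans for 10% of a 484-participant definitive trial: 0.10 × 484 = 48.4. Allowing for 20% attrition, 48.4 / 0.80 = 60.5 (or 48 / 0.80 = 60), which agrees with the stated 60. With 1:1:1:1 allocation, 60 / 4 = 15 per arm, so 3 × 15 = 45 women are in the exercise arms and 15 in control.

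**Who can meet the definition.**

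| Situation | Caused by the programme, in her view? | Counted? |
|---|---|---|
| Exerciser, problem she blames on training, treated or stops taking part | Yes | Yes |
| Exerciser, same problem, not linked by her to training | No | No |
| Exerciser, problem she blames on training, neither treated nor preventing participation | Yes | No |
| Control, any problem in the 12 randomised weeks | No programme exists | No |
| Any arm, harm from the treadmill or strength tests | Test, not programme | No |

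Counted events are therefore a subset of all harms. The count can equal the true number in the exercise arms only if every harm is attributed and every harm passes the treatment-or-participation condition.

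**Illustration for the exercise arms.** The documents give no event rate and no attribution rate, so both are assumptions, shown over a range. Let *p* be the probability that an exerciser has, within 12 weeks, a problem serious enough to meet the treatment-or-participation condition, whatever its cause. Let *s* be the share of such problems that participants attribute to the programme. Assume at most one event per woman and independence between women.

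- Expected true events = 45*p*
- Expected recorded events = 45*ps*
- Chance that none is recorded = (1 − *ps*)^45
- Chance that none truly occurs = (1 − *p*)^45

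| *p* | *s* | True events expected | Recorded events expected | Chance none recorded | Chance none occurs |
|---|---|---|---|---|---|
| 0.10 | 0.25 | 4.5 | 1.1 | 32% | 0.9% |
| 0.10 | 0.50 | 4.5 | 2.25 | 9.9% | 0.9% |
| 0.10 | 0.75 | 4.5 | 3.4 | 3.0% | 0.9% |
| 0.20 | 0.25 | 9.0 | 2.25 | 9.9% | below 0.01% |
| 0.20 | 0.50 | 9.0 | 4.5 | 0.9% | below 0.01% |
| 0.30 | 0.50 | 13.5 | 6.75 | 0.07% | below 0.01% |
| 0.30 | 0.75 | 13.5 | 10.1 | below 0.01% | below 0.01% |

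Worked line: with *p* = 0.10 and *s* = 0.50, 45 × 0.10 = 4.5 and 45 × 0.05 = 2.25; 0.95^45 = 0.099 and 0.90^45 = 0.009.

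In control the expected recorded number is 0 whatever the true rate; at *p* = 0.10 the true expectation would be 15 × 0.10 = 1.5. Milder events and test-visit harms come on top and are not in the table.

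**The case against.** The strongest defence is that the item serves to judge whether the exercise programmes can be tolerated. For that purpose, counting problems that women blame on the programme and that need treatment or stop participation is narrow but sensible. The figure misleads only if it is read as all-cause incidence. Nor are the other harms wholly invisible. Those that end participation appear, without their cause, in dropout and attendance; pain is measured in all arms before and after with the Brief Pain Inventory; sessions are supervised one to one; and exit questionnaires and interviews cover the exercise arms. A fuller protocol may also hold separate safety reporting.

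Part of this stands. It is too strong to call the harms lost. But dropout and pain scores are not an event record, the exit material omits controls, and the article fixes this definition for the analysed outcome under an unqualified label. That makes it a stated rule and not a detail left to another document.

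Four stronger readings are tempting and are not supported:

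- *That the plan is biased toward safety throughout.* This is true of the absolute count. A structural zero in controls would tilt an exercise-versus-control contrast the other way, against exercise, and the article states no such contrast for adverse events.
- *That the three programmes will be pooled.* The phrase about percentages across interventions can equally mean one percentage for each.
- *That controls can never have an event.* This holds for the 12 randomised weeks; they may join a programme afterwards.
- *That a better definition would let the pilot show which arm is safe.* With 15 per arm, zero events still has an exact two-sided 95% upper limit of 1 − 0.025^(1/15) = 22%. The article says that the pilot is not meant to be powered for between-group differences.

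**Conclusion.** The point holds as a defect in a stated definition. The planned incidence is a participant-attributed subset: it understates the absolute incidence of harms in the exercise arms, supplies no background rate from the 15 controls (25% of the 60), and does not cover the treadmill and strength tests at baseline and follow-up.

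That counted events are a subset, and that controls are excluded, follow from the text. How large the undercount is rests on assumed rates: in the scenarios shown, between a quarter and three quarters of exercise-arm events would be recorded. The reading also takes the exercise programme to mean the 12-week training and not the assessments, which is how the article describes the two.

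This is worth correcting, but it is not critical to the pilot. No effect estimate, sample size or stated decision threshold depends on the figure.

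**What to change.** Record every untoward medical event in all four arms from baseline testing to the follow-up assessment, test visits included. Put the same question at the same intervals to exercisers and controls, regardless of perceived cause. Have an existing investigator judge relatedness as a separate step. Report the number of participants with at least one event by arm, once for all causes and once for events judged related. Keep the present definition as a further line, labelled as participant-attributed.

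The cost is a short event form, used in controls as well, one relatedness judgement per event and a by-arm table. Reported rates will be somewhat higher than under the present rule. The gain is an honest description with a background rate; the text should not suggest that it establishes safety by arm.
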